**Methods:**

This is a single blind, two-arm randomised controlled trial. Participants will be business advisors who provide information, guidance and/or assistance to SME owner clients and are in contact with them at least 3 times a year. The business advisors will invite their SME-owner clients to complete 3 online surveys at baseline, 6- and 12-months. Business advisors will be randomised to one of two conditions, using a 1:1 allocation ratio: (1) MHFA with RBT; or (2) MHFA alone, and complete 3 online surveys at baseline, 2- and 6-months. Primary outcomes will be measured in the business advisors and consist of the quality of the relationship, stigmatizing attitude, confidence to offer mental health first aid, quality of life and provision of mental health first aid. Secondary outcomes will be measured in the SME owners and includes trust in their business advisors, the quality of this relationship, financial wellbeing, financial distress, psychological distress, help-seeking behaviour, and quality of life. To complement the quantitative data, we will include a qualitative process evaluation to examine what contextual factors impacted the reach, effectiveness, adoption, implementation, and maintenance of the training.

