## Measures

Demographic information including age, sex, and residential data will be collected from the registration forms. The training will have direct effects on the business advisors and in turn, have indirect effects on their SME owner-clients. For this reason, the outcomes measured from business advisors are classed as primary, and for the SME owners they are secondary.

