### Primary outcomes for business advisors

#### Quality of the relationship

At each of the data collection points, the quality of the relationship between the business advisor and their SME owner clients will be measured using a Quality of the Relationship Questionnaire. The questions will measure the business advisor’s belief about how much attention they are giving their clients, their awareness about their client’s financial and emotional needs, the quality of the advice they provide and the impact they have on their business. Ten items will be used, four are from the Relationship Flourishing Scale [24] that has a Cronbach’s alpha of 0.93, and six are from a validated newly developed tool by the principal investigators (AN, GT) with factor loadings ranging from 0.81 to 0.87. The Relationship Flourishing Scale has demonstrated acceptable concurrent, convergent and content validities [24]. All items are on a 7-point Likert scale (1 strongly disagree, 7 strongly agree) with a higher total score indicating a higher quality relationship.

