#### Quality of life

Quality of Life questions will measure the general health of the SME owners at all time points. The Short Form-12 questionnaire (SF-12) produces two summary scores – a mental component score (MCS-12) and a physical component score (PCS-12). This test has a test re-test reliability of 0.76 to 0.89 for the mental (MCS-12) and physical (PCS-12) health components [34]. Both components can discriminate among groups known to differ in their physical and mental conditions, yielding relative validities of 0.63 to 1.07 [34]. The answers are weighted and the results are presented relative to the United States population profile at the time of the original publication in 1994. A higher score for MCS and PCS indicates a better health state.

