### Sample size and power analysis

The sample size estimation was conducted using Power Analysis and Sample Size (PASS) software (version 15, PASS, NCSS, LLC). The calculations were based on detecting a small effect size (Cohen’s d = 0.20) in the business advisors primary outcome quality of the relationship as measured from an amended Relationship Flourishing Scale [24]. A sample of 786 business advisors randomly allocated (1:1) to the two study arms will achieve 80% power to detect an effect size d = 0.2 in the primary outcome or a mean difference of 1.52 between the two groups. The mean difference of 1.52 was calculated using the results from a validation study of the Relationship Flourishing Scale on 408 participants who reported a mean score of 46.36 and standard deviation of 7.60 [24]. Assuming a 20% attrition rate, we will recruit 984 business advisors. Calculations are based on a two-tailed test and α = 0.05.

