In unblinded randomised control trials, participants allocated to the control group who are aware of a more desirable treatment group, may be envious of participants in the treatment group and be less willing to complete surveys [38, 39]. Because of the appeal the new RBT may offer to business advisors, we anticipate that participants in our MHFA alone group may be unmotivated to attend training sessions, complete surveys and ultimately dropout. If such a trend is observed in this study, we may take a pragmatic decision to change the random allocation ratio to allocate more participants to MHFA alone to have equal number of participants in both groups to enhance statistical power. If such a change in the allocation ratio is needed (e.g., from 1:1 to 1:2 to account for differential attrition), the participants will no longer have an equal chance of receiving each of the treatments. Bias could also arise if participants differ in important characteristics, hence the data from these two parts of the trial will be tested for homogeneity. If any significant differences are identified, the results will be analysed separately and then combined, as in a meta-analysis [40].

All analyses will be tested with a significance level of *p* < 0.05 by using the intention to treat principle. Participants classified as lost to follow-up will be compared with the study group for baseline demographic data using ordinary t test and χ2 test for homogeneity. A sensitivity analysis will be conducted to investigate the impact of dropouts on our primary hypothesis. Magnitude of change will be estimated through effect sizes using Cohen’s guidelines, whereby a value of 0.2 denotes a small, 0.5 a medium, and 0.8 a large effect size [41–43]. Data will be entered into Excel using Microsoft Office (version 16.0.1). Professional for Windows XP and StataSE (version 16) software for statistical analysis.

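### The protocol names five, four or one primary outcome depending on the section, tests everything at p < 0.05, and does not say which primary result decides the trial

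*Protocol article*

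**What the plan says.** The Methods part of the abstract gives the primary outcomes, measured in advisors, as "quality of the relationship, stigmatizing attitude, confidence to offer mental health first aid, quality of life and provision of mental health first aid". That is five.

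The Measures section states that "the outcomes measured from business advisors are classed as primary, and for the SME owners they are secondary". Under the plural heading "Primary outcomes for business advisors" it describes four: relationship quality, stigmatising attitude, confidence, and provision of mental health first aid. Quality of life appears only among the owners' secondary outcomes: "Quality of Life questions will measure the general health of the SME owners at all time points".

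The section on sample size and power rests on one outcome, the advisors' "primary outcome quality of the relationship as measured from an amended Relationship Flourishing Scale", at two-sided alpha 0.05. The Statistics section also uses the singular for the primary outcome and the primary hypothesis.

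For advisors, the Statistics section compares the arms on three changes (baseline to 2 months, baseline to 6 months, 2 to 6 months) as the test of the hypothesis. A parenthesis then explains that test as the interaction of allocation with the 2-month measurement. The section continues: "All analyses will be tested with a significance level of" p < 0.05. It gives no adjustment, no testing order and no rule for combining the primary outcomes.

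**The concern.** Five, four and one cannot all be the number of primary outcomes. Because every analysis is tested at 0.05 and the listed advisor outcomes share the primary label without ranking, a reader cannot tell which result would make the trial positive. Any one of four or five significant results could be reported as a positive primary finding.

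The article fixes the significance level and the labels itself. A separate analysis plan that set a testing order would have to override what is printed here. The trial was registered after it started and was still recruiting at publication, so a ranking fixed before analysis is the main safeguard against choosing the favourable result afterwards.

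**Working it through.** **Inputs from the article.** Mean difference 1.52, SD 7.60, two-sided alpha 0.05, power 80%, 1:1 allocation, 786 analysed, 20% attrition, 984 recruited (Sample size and power analysis). Primary outcomes: five (abstract) or four (Measures). Advisor time contrasts: three, with 2 months singled out (Statistics).

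**Assumptions that are not in the article.** Between-outcome correlation from 0 to 0.7, and correlation 0.5 between time points.

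**1. The plan's own figure.**
- d = 1.52 / 7.60 = 0.20.
- n per arm = 2(1.960 + 0.842)² / 0.20² = 392.4, rounded up to 393, so 786 in total.
- Power at 393 per arm = Φ(0.20 × √(393/2) − 1.960) = Φ(2.804 − 1.960) = 80.06%.
- Attrition: 393 / 0.8 = 491.25, rounded up to 492 per arm, so 984.

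The stated figures reproduce for a single test at 0.05.

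**2. Familywise error, 2-month contrast only.** This assumes no true effect on any outcome and that one significant outcome is enough. With k independent tests the error is 1 − 0.95^k. The correlated values come from a normal simulation with 400,000 draws.

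| Between-outcome correlation | 4 outcomes | 5 outcomes |
|---|---|---|
| 0 (formula) | 18.5% | 22.6% |
| 0.3 | 17.3% | 20.8% |
| 0.5 | 15.6% | 18.3% |
| 0.7 | 13.1% | 14.9% |

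This is about 2.6 to 4.5 times the nominal 5%.

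**3. If all three contrasts also counted.** The same simulation gives about 12% for one outcome alone. For four outcomes it gives 29% (correlation 0.7) to 41% (independent outcomes), and for five 33% to 48%.

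**4. Price of keeping four or five co-equal primaries.** Bonferroni, one contrast per outcome, d = 0.2:
- Four outcomes: alpha = 0.05/4 = 0.0125. Power at 786 = Φ(2.804 − 2.498) = 62%. For 80% power, 1116 analysed, and 1116 / 0.8 = 1395 recruited.
- Five outcomes: alpha = 0.05/5 = 0.01. Power at 786 = Φ(2.804 − 2.576) = 59%. For 80% power, 1168 analysed, and 1168 / 0.8 = 1460 recruited.

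**The case against.** The best defence is that the sample-size section and the singular wording in Statistics already make relationship quality the one confirmatory outcome, and that the parenthesis fixes 2 months. On that reading the error rate of the deciding test is 5% and the fault is one of labelling. This is a fair reading, but it makes the abstract and the Measures section wrong, so the text needs correcting either way. The inflation also depends on any single success being enough. A rule that all primaries must succeed would not inflate alpha, but none is stated.

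Four stronger inferences are tempting, and the article does not support them.
- *Three contrasts per outcome are all confirmatory, so 12 tests give 46%.* The parenthesis can confine the hypothesis test to 2 months. The 46% also treats as independent contrasts that come from the same people and are linearly dependent.
- *Stigma and provision each split in two, giving six primary outcomes and 26.5%.* The article says that summary scores will be produced for two stigma dimensions. It does not make each a primary outcome with its own test, and it does not state separate primary tests for the two provision scores.
- *The 80% power applies only to the relationship scale.* The 786 gives about 80% for any roughly continuous score at d = 0.2 and alpha 0.05. Only the raw difference of 1.52 belongs to that scale.
- *Advisor quality of life is a missing measure.* The advisor hypotheses in the Background match the four outcomes in Measures, which points to a slip in the abstract. Supplementary file 3, which lists further survey outcomes, is not shown.

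**Conclusion.** The concern holds. The primary set is contradictory, every analysis is tested at 0.05, no decision rule is given, and the deciding time point is ambiguous. If any one primary success counts, the familywise error at 2 months is about 13% to 23%. That range rests on a global null, four or five outcomes, and an assumed between-outcome correlation of 0.7 down to 0. It is higher if the other contrasts also count, and it is 5% if relationship quality at 2 months alone decides. The sample size is not in error: it suits a single test at 0.05 but does not cover four or five alpha-adjusted primaries at 80% power.

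**What to change.** Before analysis, name one primary test: advisor-rated relationship quality, between-arm difference in change from baseline to 2 months. It is the outcome already powered and the time point already singled out. Class stigma, confidence, provision and the other time contrasts as secondary, with Holm adjustment or confidence intervals only. An ordered test that starts with relationship quality would serve equally. Reconcile advisor quality of life between the abstract and Measures, by removing it from the primary list or by describing it as an advisor measure if advisors do complete it.

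The cost is more than wording. Some outcomes lose primary status, and the article's own rules (Ethical principles) require ethics approval and communication to the registry, while recruitment is under way. The 786 analysed, 984 recruited and alpha 0.05 do not change.

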### Qualitative analysis

The structured interviews will be audiotaped and transcribed, then combined with field notes to form a narrative database to be analysed thematically using NVivo (QRS International Version 11) for Windows. A codebook will be created by LS and SB to help identify blocks of texts that represents one of the five RE-AIM constructs. The results of the first round will be compared and any discrepancies will be adjudicated by CEV. A more detailed second round of coding by LS and SB will identify specific themes within these blocks of texts. The results will be discussed by LS, SB and CEV, and a consensus will be reached on the emerging themes. The findings from the qualitative analysis will be used to complement those from the quantitative analysis, so we can better understand what worked for whom in which circumstances.

## Discussion

The aim of this paper is to describe how we will: 1) deliver and evaluate an RCT designed to assess the effectiveness of combining RBT with MHFA for business advisors and their SME owner clients, and 2) conduct a process evaluation to assess what contextual factors impacted the reach, effectiveness, adoption, implementation, and maintenance of the program. To the best of our knowledge, this is the first study to test the effectiveness of using business advisors as a conduit for providing SME owners with mental health support. We believe this approach will ensure SME owners who need help are more likely to receive it.

One of the key strengths of the current research is that the RCT has been developed by a multi-disciplinary team of researchers (spanning the accounting and management sciences, public health and clinical psychiatry), working in conjunction with accounting and bookkeeping member bodies (IPA, CPA, CAANZ, ICB), influential policy makers (Beyond Blue, WorkSafe Victoria, The Treasury) and Australia’s largest provider of MHFA training services (MHFA Australia). The strong partnerships with the professional member bodies are particularly important for ensuring that the trial could be delivered on a sector-wide scale and as part of the CPD training that accountants and bookkeepers are expected to undertake as part of their professional accreditation requirements. The accreditation points gained from the training will help incentivise business advisors to take part and to increase the likelihood that the required number of participants are recruited. In addition, collaborating with member bodies and policy makers will help the authors identify future knowledge translation and sustainability opportunities to address mental wellbeing in the business sector.

The COVID-19 pandemic has increased the likelihood that SME owners will contact their accountant and bookkeeper in heightened states of distress. While this increased demand reinforces the need to equip business advisors with the skills to work with clients experiencing high levels of stress, the anticipated surges in business advisor workloads also represent a key barrier to advisers undertaking the training. To address this, the program has been designed with the business advisors’ operational needs in mind (e.g., fully online, range of training dates offered, incentivised participation). The process evaluation and ongoing dialogue with the professional organisational bodies will also identify any recruitment and retention problems early and to implement appropriate mitigation strategies as soon as possible.

Another strength of this study is using a rigorous RCT design to assess the benefit of offering RBT in combination with MHFA compared with MHFA alone. This design will minimise confounding factors, such as lockdowns during the pandemic, that could have a significant impact on the outcomes. The length of follow-up in business advisors (5-months post training) and SME owners (11-months post training) will also inform whether there are any long-term benefits. Another unique component of this RCT is the recruitment of SME owner clients, who as end-users or beneficiaries of the training, will provide insight into the effectiveness of the training. However, the recruitment of SME owners is expected to be difficult largely because of the busy, all-consuming nature of their role (e.g., long work hours, burden of responsibility). It is for this reason, we introduced gift voucher incentives for SME owners to complete the surveys and to participate in interviews. Another strength of the study is its large sample size predicated on conservative effect size estimates.

To date, the business environment has not been leveraged as a platform for delivering mental health interventions, notwithstanding the major impact of mental health conditions on the sector. The findings from this research will provide important information on the benefits of incorporating a mental health literacy program like MHFA within a more mainstream client relationship building program. If the current research supports the hypothesis that the combined approach leads to more beneficial outcomes than MHFA alone, then the approach could be adopted by other small business intermediaries (e.g., human resource consultants, lawyers, bankers). Similarly, these findings could also be used to inform how business accounting and finance students are trained prior to entering the workforce (i.e., via undergraduate and post-graduate degrees). Finally, the process evaluation will be critical for developing a more detailed understanding of the range of factors that helped or hindered program effectiveness and the success of its roll-out. This information, along with the outcomes of the RCT, can be used to guide efforts to enhance program reach, adoption, implementation, and maintenance in the business sector.

## Data Availability

The data for this study will be made available upon request to [name]: [contact]. The research team will make the findings publicly available at national and international conferences, and in peer-reviewed journal publications.

## Abbreviations

CONSORT: Consolidated standards of reporting trials
GEE: Generalised estimated equation
MHFA: Mental health first aid
RCT: Randomised control trial
RE-AIM: Reach, effectiveness, adoption, implementation, maintenance
RBT: Relationship building training
SME: Small-medium entrepreneurs
